#### Safety assessment

The incidence of treatment-emergent adverse events (AEs) will be monitored throughout the entire *Tuina* treatment. Common AEs include local skin damage and rash. Should an AE occur during treatment, the time of occurrence, severity, progress, and treatment of the AE will be recorded in detail. If any serious AE occurs the Principal Investigator and the Institutional Review Board will be informed immediately and direct action will be taken immediately.

#### Unexpected event processing

In the event of damage to the skin, manipulations shall immediately cease. If necessary, affected areas will be treated with an anti-inflammatory cream. For severe cases, antibiotics will be used to prevent infection.

In the event of skin redness or a rash occurring, manipulations shall immediately cease. For severe skin rashes, treatment will be as provided as deemed appropriate by a pediatrician.

### Participant timeline

Figure 2 demonstrates the overall schedule for participant recruitment, intervention, assessment and follow-up, based on the SPIRIT figure.

**Fig. 2 Fig2:**
[figure not shown]
Study schedule for recruitment, interventions, outcome measurements and data collection

### Sample size estimation

This study includes two primary outcomes: diarrhea days and diarrhea times. Sample size was estimated based on the two primary outcome measures. Estimation according to diarrhea days was based on results from previous relevant literature [29], which established diarrhea days in children as 2.1 days after receiving *Tuina* plus usual care. The estimated standard deviation is 1.4. Diarrhea days in children after receiving usual care is 4.0 and the estimated standard deviation is 3.5. On the basis of a 5% false-positive error rate (α = 0.05, two-sided) and 90% power (β = 0.1), sample size was estimated using PASS11 software. A sample size of at least 35 participants should be recruited in each group. Assuming an approximate 20% dropout rate, a total of 84 (70 plus 20% is 84) participants should be enrolled in the trial (42 in each group).

Estimation according to diarrhea times was likewise based on reference from previous relevant studies [30], which established diarrhea times in children as 4.1 times per day after receiving *Tuina* plus usual care. The estimated standard deviation is 1.5. Diarrhea times of children after receiving usual care is 6.2 times per day and the estimated standard deviation is 4.8. On the basis of a 5% false-positive error rate (α = 0.05, two-sided) and 90% power (β = 0.1), sample size was estimated using PASS11. A sample size of at least 51 participants should be recruited in each group. Assuming an approximate 20% dropout rate, a total of 122 (102 plus 20% is 122) participants should be enrolled in the trial (61 in each group).

Based on these results, we chose the larger number sample size, that is 122 participants, for the estimated final trial sample size.

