#### Primary outcomes

The primary outcome measure for diarrhea will be diarrhea days from baseline and diarrhea times on the third day. The assessment of diarrhea days refers to the period of days from baseline to the first day that diarrhea is reduced to less than or equal to two times per day throughout the treatment and follow-up period. Diarrhea times will be evaluated on the third day of intervention. In this study, we define the baseline and the first day of intervention as the same day.

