### Statistical analysis

Statistical analysis will be performed by trial statisticians who are blinded to the group allocation using SPSS Statistics Software 19.0 and SAS version 9.4. All statistical tests will be two sided with a significance level of 0.05. We will summarize the social demographic characteristics of the participants by groups using simple descriptive statistics. Normally distributed quantitative variables will be described by means and standard deviation and non-normally distributed variables will be described by median and interquartile range. In addition, the 95% confidence intervals will be presented when calculating the difference in means between groups. For categorical variables, numbers and percentages will be presented.

We intend to use the intention-to-treat and per-protocol approach to analyze data. For intention-to-treat analysis, all participants will be included in the analysis according to the group to which they were originally randomized, regardless of whether they complete the treatment or adhere to the protocol. For per-protocol analysis, only participants who complete the whole treatment (i.e., those who receive treatments once per day for 3 consecutive days) will be included. Between-group comparisons will be performed using two-sample *t* tests for normally distributed data and Mann–Whitney *U* test for non-normally distributed data. For categorical variables, chi-square tests or Fisher’s exact test will be used for group comparison.

Multivariable regression analysis will be performed to analyze the associations between pediatric *Tuina* and primary or secondary outcomes with adjustment for covariates including social demographic characteristics, birth characteristics, medication history, and so forth. Missing data will be imputed through multiple imputation using chained equations.

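### Two primary outcomes each take the full two-sided 0.05, and the protocol does not say whether efficacy needs either or both; under an either rule the false-positive rate is about 7.0–9.75%, not 5%

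*Protocol article*

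**What the plan says.** The Primary outcomes section reads: "The primary outcome measure for diarrhea will be diarrhea days from baseline and diarrhea times on the third day". Days is the time from baseline to the first day with at most two stools; times is the count on day 3 of the intervention.

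The Sample size estimation section confirms that there are two primaries ("This study includes two primary outcomes: diarrhea days and diarrhea times") and runs one calculation for each. Both start from the same premise: "On the basis of a 5% false-positive error rate (α = 0.05, two-sided) and 90% power (β = 0.1". The results are 35 per group for days and 51 for times. The larger is kept and raised by 20% to 122 children, 61 per group.

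The Statistical analysis section adds: "All statistical tests will be two sided with a significance level of 0.05". On analysis sets it says: "We intend to use the intention-to-treat and per-protocol approach to analyze data". It then describes two-sample comparisons and, separately, multivariable regression for both primary and secondary outcomes. No section gives a success rule for the pair, an order of testing or an alpha adjustment.

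**The concern.** With two primary outcomes, the success rule decides what the stated 5% and 90% mean. If either outcome suffices, there are two chances of a false claim, so the error rate is above 5%. If both are required, the error rate is safe, but the relevant power is the chance of winning both, which cannot exceed that of the weaker outcome. The protocol gives 5% and 90% for each outcome alone and leaves the rule open, so neither figure describes the trial's overall conclusion. The rule could also be chosen once the results are known. That matters here because the closing discussion says the trial is expected to demonstrate efficacy.

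**Working it through.** **Inputs (Sample size estimation).**
- Days: means 2.1 and 4.0 (difference 1.9), SDs 1.4 and 3.5; stated 35 per group.
- Times: means 4.1 and 6.2 (difference 2.1), SDs 1.5 and 4.8; stated 51 per group.
- Two-sided 0.05, 90% power, 1:1 allocation.
- Correlation between the outcomes: not given; 0 to 0.9 is assumed.

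**1. The plan's own figures.** n per group = (z_α + z_β)² × (s₁² + s₂²) / d².

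| | Days | Times |
|---|---|---|
| (s₁² + s₂²)/d² | 14.21/3.61 = 3.936 | 25.29/4.41 = 5.735 |
| Two-sided, (1.960 + 1.282)² = 10.507 | 41.4 → 42 (Welch t: 43) | 60.3 → 61 (Welch t: 62) |
| One-sided, (1.645 + 1.282)² = 8.564 | 33.7 → 34 (Welch t: 35) | 49.1 → 50 (Welch t: 51) |
| Stated | 35 | 51 |

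The stated numbers are not reproduced by the stated two-sided test. They match a one-sided 5% Welch test exactly.

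**2. Either outcome enough.** Family-wise error = 1 − P(|Z₁| < 1.96 and |Z₂| < 1.96), with Z₁ and Z₂ bivariate normal. At correlation 0 this is 1 − 0.95² = 9.75%.

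| Correlation | 0 | 0.3 | 0.5 | 0.7 | 0.8 | 0.9 |
|---|---|---|---|---|---|---|
| Family-wise error | 9.75% | 9.5% | 9.1% | 8.3% | 7.8% | 7.0% |

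**3. Both needed.** Expected z at 51 per group:
- Days: 1.9/√(14.21/51) = 3.60; power Φ(3.60 − 1.96) = 94.9% (Welch 94.4%).
- Times: 2.1/√(25.29/51) = 2.98; power Φ(2.98 − 1.96) = 84.7% (Welch 83.5%).
- Joint power at correlation 0: 0.949 × 0.847 = 80.4% (Welch 78.8%). At correlation 0.9: 84.4%.

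**4. Where the shortfall comes from (normal approximation).** The sizing of times alone loses 90 − 84.7 = 5.3 points. Requiring both then costs 84.7 − 80.4 = 4.3 points at correlation 0 and 84.7 − 84.4 = 0.3 at 0.9.

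As a cross-check, take the protocol's 90% at face value. Times has 90% at 51. Days, with 90% at 35, has Φ(3.242 × √(51/35) − 1.96) = 97.5% at 51. Joint power is then 0.90 × 0.975 = 87.7% at correlation 0, and at most 90%.

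**5. Power under Holm at 51 per group.** An outcome is claimed if its own z exceeds 2.241 (two-sided 0.025), or if it exceeds 1.96 while the other exceeds 2.241.
- Days at correlation 0: 0.913 + (0.949 − 0.913) × 0.771 = 94.1%; by the bivariate normal, 91.6% at 0.9.
- Times at correlation 0: 0.771 + (0.847 − 0.771) × 0.913 = 84.0%; between 83.5% and 84.0% over the whole range.

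**The case against.** **Left to the analysis plan.** A condensed article can leave multiplicity detail to an analysis plan. That would answer mere silence, but this article is not silent on alpha: it gives the full 0.05 to each primary in the sizing and 0.05 to every test. An analysis plan that divided alpha would depart from the stated design basis.

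**A both rule may be meant.** The two measures are joined by 'and' under a singular primary outcome measure, and each is sized at full alpha with the larger number kept. That fits a both rule, which inflates nothing. This objection stands in part: an inflated error rate is not demonstrated, only permitted. The text does not settle which rule applies.

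**Independence is implausible.** Both outcomes come from the same daily stool counts, so positive correlation is likely. This stands: 9.75% is the upper limit for one analysis set, and the near-doubling a reader might infer holds only there.

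**Counting analyses.** A reader might multiply two outcomes by two analysis sets by unadjusted and adjusted models and say that eight results could each carry the claim. The protocol does not support this. It nowhere says that a per-protocol or regression result would establish efficacy, and it describes regression as examining associations. Ranking the sets is also commonly left to an analysis plan. A second set adds error only if a win in either set counts.

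**Conclusion.** The protocol gives each of two primary outcomes the full two-sided 0.05 and has no rule for combining them, so the error rate of the efficacy claim is undefined. Under an either rule it is about 7.0–9.75%, assuming correlation 0.9 to 0. Under a both rule alpha is sound, and joint power at 51 evaluable per group is about 79–84%, given the protocol's own means and SDs. The low end is the Welch product at correlation 0.

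It would be wrong to infer that the missing rule is what pulls joint power well below 90%. Diarrhea times alone has only about 85% power at 51 per group under the stated two-sided test, which is a separate sample-size matter. Adding a rule would not recover those roughly 5 points.

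**What to change.** Before unblinding, state one rule for the pair in the Statistical analysis section:
- **Fixed sequence**, for example diarrhea days at two-sided 0.05, then diarrhea times at 0.05 only if days is significant; or
- **Holm** across the two outcomes; or
- **both required**, each at 0.05, with the joint power restated as about 79–84% at 51 evaluable per group.

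Base that test on the intention-to-treat set and label per-protocol and regression results as supportive.

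The cost is a few sentences, and error control needs no extra patients. Each choice has a price. With days first in a fixed sequence, power for days stays at about 94–95%, but times, the outcome that set 122, can be claimed only with the joint power of about 79–84%. The order is a choice the protocol does not make. Holm lowers power for days by 0.8–3.3 points (to 91.6–94.1%) and for times by about 1 point. Under a both rule, 90% joint power would need 61–65 evaluable per group (normal approximation, correlation 0.9 to 0), or 77–82 enrolled after dividing by 0.8, against 61 now. The Trial status section has recruitment ending in September 2019, so restating the power may be the only practical course there.

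### The group sizes of 35 and 51 do not give 90% power at two-sided 0.05; they match a one-sided calculation, and diarrhea times has about 84% power at the planned 51 per group

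*Protocol article*

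**What the plan says.** The section Sample size estimation sizes the trial separately for two primary outcomes and takes the larger result. Both calculations use the same error rates: "On the basis of a 5% false-positive error rate (α = 0.05, two-sided) and 90% power (β = 0.1").

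- **Diarrhea days:** mean 2.1 (SD 1.4) with Tuina and 4.0 (SD 3.5) with usual care. Result: "A sample size of at least 35 participants should be recruited in each group". Adding 20% for dropout gives 84 in total.
- **Diarrhea times:** mean 4.1 per day (SD 1.5) with Tuina and 6.2 per day (SD 4.8) with usual care. Result: "A sample size of at least 51 participants should be recruited in each group". Adding 20% gives 122 in total, 61 per group, and this becomes the trial size.

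The section Statistical analysis fixes the tests: "All statistical tests will be two sided with a significance level of 0.05". It names the two-sample t test, or the Mann–Whitney test if the data are not normal. The article mentions no one-sided test.

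**The concern.** Means, SDs, α, sidedness, power and allocation ratio are all printed, so the group sizes can be checked directly. Both come out about 18% below what a two-sided test needs: (43 − 35)/43 = 19% and (62 − 51)/62 = 18%. This is too much for rounding or for the choice between normal and t formulas.

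The error falls on the outcome that determines N. A non-significant day-3 result would be read as coming from a trial with a 10% chance of missing the assumed effect, when the planned evaluable number leaves about 16% to 17%. The discussion also lists obtaining estimates for a sample size calculation as a feasibility criterion, so a later trial might reuse this calculation.

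**Working it through.** **Inputs** (Sample size estimation; 1:1 allocation from Study design)

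| | Days | Times |
|---|---|---|
| Difference in means, d | 4.0 − 2.1 = 1.9 | 6.2 − 4.1 = 2.1 |
| s₁² + s₂² | 1.4² + 3.5² = 14.21 | 1.5² + 4.8² = 25.29 |
| d² | 3.61 | 4.41 |
| Stated n per group | 35 | 51 |

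**Step 1: normal approximation.** n per group = (z_α + z_β)² (s₁² + s₂²) / d², with z_β = 1.2816 for 90% power.

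- Two-sided 0.05: (1.9600 + 1.2816)² = 10.507. Days: 10.507 × 14.21 / 3.61 = 41.4, so 42. Times: 10.507 × 25.29 / 4.41 = 60.3, so 61.
- One-sided 0.05: (1.6449 + 1.2816)² = 8.564. Days: 8.564 × 14.21 / 3.61 = 33.7, so 34. Times: 8.564 × 25.29 / 4.41 = 49.1, so 50.

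**Step 2: exact t-test calculation.** Power = 1 − F(t_crit; df, δ), where F is the noncentral t distribution and δ = d / √[(s₁² + s₂²)/n]. For unequal variances (Welch), df = (n − 1)(s₁² + s₂²)² / (s₁⁴ + s₂⁴). For the pooled test, df = 2n − 2. The smallest n per group reaching 90% is:

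| | Stated | One-sided Welch | One-sided pooled | Two-sided Welch | Two-sided pooled |
|---|---|---|---|---|---|
| Days | 35 | **35** | 35 | 43 | 43 |
| Times | 51 | **51** | 50 | 62 | 62 |

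The one-sided Welch calculation reproduces both stated figures exactly. One child fewer per group falls below 90% each time (34: 89.4%; 50: 89.9%). The two-sided calculation reproduces neither.

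**Step 3: other routes to 35 and 51 at 90% two-sided.** Mann–Whitney efficiency adjustments give 46 and 65 (normal), 40 and 57 (logistic) or 29 and 42 (double exponential). Using the plain average of the two SDs comes nearest (35 and 48 by z, 36 and 49 by t). It does not match both figures, and it is not a valid variance for this comparison. Rounding of the printed inputs does not explain the gap either. At the most favourable rounding for diarrhea times (d = 2.2, SDs 1.45 and 4.75), the Welch test still needs 56.

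**Step 4: two-sided power at the numbers the trial can have.** Example for times at n = 51: δ = 2.1 / √(25.29/51) = 2.982. Welch df = 50 × 25.29² / (1.5⁴ + 4.8⁴) = 59.7, so t_crit = 2.0005 and power is 83.5%.

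| Evaluable per group | Times: Welch / pooled / z | Days: Welch / pooled |
|---|---|---|
| 35 | – | 83.1% / 83.6% |
| 49 (61 × 0.8 = 48.8) | 82.0% / 82.5% / 83.2% | 93.5% / 93.7% |
| 51 | 83.5% / 84.0% / 84.7% | 94.4% / 94.6% |
| 61 (no dropout) | 89.6% / 89.9% / 90.4% | 97.3% / 97.4% |
| 62 | 90.1% (Welch) | – |

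A simulation of 50,000 trials for times at n = 51 gave 83.8% (Welch) and 84.2% (pooled).

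**The case against.** Three points deserve an answer.

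*The cause is inferred.* The article does not say that a one-sided setting was used, and the software output is not shown. For diarrhea times the match is exact only with Welch degrees of freedom; the pooled test gives 50. This stands as a caution about attribution. An exact match on two outcomes is strong evidence but not proof. The shortfall does not depend on it, because the stated two-sided inputs do not give 35 or 51 by any valid route tried.

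*The trial enrols 61 per group, not 51.* If every child is evaluable, power for diarrhea times is 89.6% to 89.9% by t test (90.4% by the normal approximation), very near the claim. So the 83% to 84% figure is conditional on 51 evaluable per group. But the plan itself expects about 20% dropout and presents 51 as the number that gives 90%. The extra children were budgeted for loss and cannot also make up the sizing error. Multiple imputation keeps all 61 in the intention-to-treat analysis but does not restore the lost information.

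*The consequence is limited.* Type I error, estimates and confidence intervals are unaffected. Diarrhea days is well powered, and diarrhea times stays above 80%. Recruitment was due to end in September 2019, before the article appeared, so the sample cannot change. All of this is true. It makes the remedy a reporting correction, but the power statement remains wrong.

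**Conclusion.** The concern holds. On the protocol's own assumptions (its means and SDs, 1:1 allocation, t test), 90% power at two-sided 0.05 needs 43 per group for diarrhea days and 62 for diarrhea times. The stated 35 and 51 are the one-sided 0.05 answers, and they conflict with both the sample size section and the analysis section.

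For diarrhea times, two-sided power is about 84% with 51 evaluable per group and about 82% if a full 20% of the 122 are lost. By t test it is just under 90% even if none are lost. The shortfall is confined to this outcome, since diarrhea days has about 94% at 51 per group.

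These figures take the assumed effects and SDs as given and treat the data as normal. They say nothing about whether those assumptions are realistic.

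**What to change.** Revise Sample size estimation as follows:

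- Give the two-sided requirements for 90% power as 43 evaluable children per group (diarrhea days) and 62 (diarrhea times).
- Withdraw the 90% claim for the trial as sized. State instead that 122 randomized children, with 51 evaluable per group, give about 84% power for diarrhea times and 94% for diarrhea days at two-sided 0.05.
- Preferably add the range for diarrhea times: about 82% at 49 per group (20% dropout) and just under 90% at 61 (none).
- Keep N at 122 and keep all tests two-sided.

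This is wording only. It needs no extra patients and no change to the analysis. The cost is a less favourable power statement, which should also be carried into the results paper.

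### The 20% dropout allowance is added on top instead of divided out, so 122 children do not leave the required 51 per group

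*Protocol article*

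**What the plan says.** The section Sample size estimation in the protocol article sizes the trial separately for its two primary outcomes and takes the larger result.

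- **Diarrhea times.** The inputs are a mean of 4.1 per day (SD 1.5) with Tuina plus usual care, and for the control arm: "Diarrhea times of children after receiving usual care is 6.2 times per day and the estimated standard deviation is 4.8". The error rates are given as "On the basis of a 5% false-positive error rate (α = 0.05, two-sided) and 90% power (β = 0.1". The result is "A sample size of at least 51 participants should be recruited in each group", that is 102 in total. With about 20% dropout the section arrives at "a total of 122 (102 plus 20% is 122) participants should be enrolled in the trial (61 in each group".
- **Diarrhea days.** The requirement is 35 per group, 70 in total. With the same dropout rate, "a total of 84 (70 plus 20% is 84) participants should be enrolled in the trial".

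The larger figure, 122, becomes the final trial size. It is repeated in the Abstract and under Participants.

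**The concern.** The bracketed working shows how dropout was handled: 20% of the evaluable number was added to it. Dropout, however, is a proportion of those enrolled. If 20% of the enrolled children are lost, 80% remain, so enrolment must be the required number divided by 0.8. Adding 20% always falls short, because 1.2 × 0.8 = 0.96: only 96% of the required number is left.

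At stake is whether the stated enrolment keeps the stated minimum at the stated dropout rate. The error sits in the diarrhea-times calculation, which sets the size of the whole trial.

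**Working it through.** **Inputs** (all from Sample size estimation): required evaluable number 51 per group (102) for times and 35 per group (70) for days; dropout 20%; times 4.1 (SD 1.5) against 6.2 (SD 4.8), difference 2.1; days 2.1 (SD 1.4) against 4.0 (SD 3.5), difference 1.9; 1:1 allocation.

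**1. Reproduce the plan's enrolment figures.** Multiplying by 1 + 0.20:
- times: 102 × 1.2 = 122.4, stated as 122
- days: 70 × 1.2 = 84, as stated

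Both figures reproduce, so the method is not in doubt.

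**2. Apply the plan's own dropout rate to that enrolment.**
- times: 122 × 0.8 = 97.6, or 48.8 per group, against 51 required
- days: 84 × 0.8 = 67.2, or 33.6 per group, against 35 required

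**3. Enrolment that would keep the required number**, N / (1 − 0.20):
- times: 102 / 0.8 = 127.5, so 128 (64 per group), 6 more than 122
- days: 70 / 0.8 = 87.5, so 88, 4 more than 84

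**4. Largest dropout that 122 can absorb:** 1 − 102/122 = 16.4%.

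**5. Effect on power.** Unequal-variance (Welch) t test with n per group, noncentrality = difference / √((SD₁² + SD₂²)/n). For times the sum of variances is 1.5² + 4.8² = 2.25 + 23.04 = 25.29. At n = 51 the noncentrality is 2.1/√(25.29/51) = 2.98; at n = 49 it is 2.1/√(25.29/49) = 2.92.

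| n per group | Times, two-sided 0.05 | Times, one-sided 0.05 | Days, two-sided 0.05 |
|---|---|---|---|
| 48 | 81.2% | 88.8% | 93.0% |
| 49 | 82.0% | 89.3% | 93.5% |
| 51 | 83.5% | 90.4% | 94.4% |

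The one-sided column is shown because that is the setting in which the stated 51 reproduces exactly (as does 35 for days). At the two-sided 0.05 that the text states, 90% power needs 62 per group for times by the same method. That is a separate error in the same section. The dropout step is measured by the change from 51 to 49 within a column: 1.5 points two-sided, 1.1 points one-sided.

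**The case against.** The arithmetic is not in dispute; the objections concern weight.

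- **The effect is small.** About two children per group and 1 to 1.5 points of power are probably less than the uncertainty in SDs taken from earlier studies, and the rate is called approximate. This stands as to size. It does not make the statement right: 122 covers 16.4%, and the plan says 20%.
- **Most of the gap to 90% has another cause.** This stands. Of the 8 points between 90% and 82%, about 6.5 come from the sidedness and must not be counted here.
- **128 is not a sound target either.** This stands. It corrects only the dropout step. With 62 per group as the base (124 in total), division by 0.8 gives 155, or 156 for equal groups.
- **The diarrhea-days slip changes nothing.** This stands, since 84 was never adopted and 48 to 49 per group is well above 35.
- **Dropouts are not simply lost.** Under Statistical analysis, all randomized children enter the intention-to-treat analysis with multiple imputation, and diarrhea times are read on day 3, when losses may be lower than over 14 days. This softens the point only in part. The sample size section treats dropouts as lost, otherwise it would need no allowance. Imputation does not fully restore the missing information, and the per-protocol analysis is limited to children who complete all three treatments. The feasibility criteria in the Discussion accept 80% of visits completed, so a loss near 20% is within what the plan tolerates.

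**Conclusion.** The point holds. At the plan's own 20% dropout, 122 enrolled children leave about 49 per group and not the 51 the plan requires; the shortfall in enrolment is 6 children. Taken alone, the step costs about 1 to 1.5 points of power for diarrhea times: 83.5% to 82.0% at two-sided 0.05, or 90.4% to 89.3% under the one-sided setting that reproduces 51. So even on the calculation most favourable to the plan, power ends just under the stated 90%. Diarrhea days is not at risk, with 93% or more at 48 to 49 per group.

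These figures rest on the planning means and SDs in the protocol article, on a Welch t test, on dropout being equal in the two groups, and on children who drop out contributing no data.

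**What to change.** Recruitment was due to end in September 2019 (Trial status), so the practical remedy is to keep 122 and describe it correctly. Suggested text for Sample size estimation:

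> Enrolment of 122 children allows for about 16% dropout. With 20% dropout, about 97 children (48 to 49 per group) would be evaluable, which gives about 82% power for diarrhea times and about 93% for diarrhea days at a two-sided significance level of 0.05.

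In the diarrhea-days paragraph, replace 84 (42 per group) by 88 (44 per group).

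Make this change in the same edit that resolves the sidedness of the calculation. Otherwise the 82% would stand beside an uncorrected claim of 90% power with 51 per group, and the section would contradict itself in a new way.

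The cost is wording only: no additional children, no change to conduct or analysis, and a somewhat less favourable stated power.
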